#### AI modeling

Our assessment tool is based on dynamic data modeling that includes the temporal aspect of multimodal signals in relation to the target variables, i.e., the behavioral trajectories of the children during the play phase. The interest of the dynamic approach is the number of samples processed per observation and per run, which increases the number of learning data.

This approach allows to analyze more signals in a single assessment and to synchronize them to obtain finer behavioral profiles that are sensitive to the inherent variability of individual performances and abilities than the classical approach where for each run all signals are summarized to a single observation, and consequently there will be few learning observations (one label per run). Recurrent neural networks and transformers have been chosen as prediction models for time series.

The prediction AI model consists of three main steps:

▪ The first one is to merge the features from the multiple signals, and structure them as multivariate time series ready to be used by machine learning models, since the prediction approach discussed is dynamic and will consider the dynamic aspect of the data. High-level feature extraction will be validated by expertise of psychologists and physicians. This choice is mainly for the explicability of the outputs of the system since it allows to detect the most relevant features and to find the causal relationships between them the target variables and the input features. This part can include already trained AI models. For example, the use of already trained deep learning networks for the detection of face and eye points, head position, etc., … This extraction also includes domain expertise. The latter is very important in this domain, i.e., high-level feature extraction from multimodal signals, as it is used to design what to extract in such a way that it is interpretable and effective for prediction based on human experience.▪ A second step of variable selection will be applied to reduce the set of input variables and to identify the most relevant features. This step will also be useful for the output of the prediction module to detect causal relationships between high-level behavioral characteristics and the variables to be predicted, for example, children’s attention scores. On a technical level, the methods applied in this stage are part of the “feature selection” methods and can be supervised or unsupervised machine learning methods. In the learning phase, several methods can be tested to find the best one for each attention score.▪ The third step is summarized in the prediction module which consists in applying prediction models with a sequence-to-label strategy, since the novelty of this tool will be to predict the scores of cognitive, metacognitive and behavioral functions in a dynamic way, i.e., to predict an attention score at an instant of time according to the past temporal sequences of the features extracted in the second step of the prediction module. The length of the sequences will be studied in more detail soon depending on the size of the available behavioral signals and will be adjusted in such a way as to improve the predictions. In this context, the classifiers used will be recurrent neural networks, for example the LSTM (Long Short-Term Memory) network, and transformers. A second feature can be easily added to the prediction tool which consists in classifying the children (NDD/neurotypical) starting only from the high-level features extracted from the raw behavior signals, without the need for labels (attention scores). In this case, unsupervised learning models of the “clustering” type are applied.

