## Discussion

We have described EPIDIA4Kids, a study protocol to evaluate how multimodality biometry relying on digital epidemiology can give insight into brain functioning in children aged 7 to 12 years. While they are playing psychometric games on an unmodified tablet, multi-stream data will be collected from 400 children volunteers independently of NDD diagnosis.

Multivariate linear models for brain functioning scores will be obtained by using supervised machine/deep-learning and cross-validation. Those models will include variables from the collected biometric data such as emotion estimates, eye-tracking features, digit-trajectories, correction rates and response time during game’s performances. Each brain functioning scores estimated by each biometric model will be agreed with each score of one or some questionnaires. This multimodality approach (73) reflects the recent advances in both quantity and quality of data available since Information & Communication Technology (ICT) and Internet of Things (IoT) brings high potential for improved accuracy at cost-efficiency (24, 28). Machine learning and AI applied to NDDs may open valuable route to examine heterogenous symptoms in pediatric population and at individual level, by integrating multimodality dimensions in prediction models, such as social, environmental, and structural determinants (74–76). Furthermore, the models can handle for missing data and larger numbers of interactive predictors. The so-called digital epidemiology could thus provide support more accurate and objective diagnostic and therapeutic decision making to health practitioners in their practice.

However, while we aim at building comprehensive datasets to create meaningful metrics of cognition, emotions and behaviors based digital epidemiology, we will carefully review data quality to lower response bias (e.g., youth’s illectronism, intra-and inter-examiner variance) by, for instance, minimizing heterogeneity of hardware implementation, and AI-related bias (e.g., over/underfitting). Furthermore, these *de novo* biometrics will require mix adjustment to ensure that observed differences in outcomes are relevant to the actual clinical categorization.

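### The AI plan counts samples within a child as added learning data, although each score has only about 400 independent children behind it, and it names cross-validation without fixing the child as the unit of splitting

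*Protocol article*

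**What the plan says.** Protocol article, AI modeling: the dynamic approach is recommended because "The interest of the dynamic approach is the number of samples processed per observation and per run, which increases the number of learning data". It is set against a classical approach in which each run is reduced to one summary, and "consequently there will be few learning observations (one label per run").

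The same section fixes the type of model: "Recurrent neural networks and transformers have been chosen as prediction models for time series". The third step consists in "applying prediction models with a sequence-to-label strategy", and the aim is "to predict an attention score at an instant of time according to the past temporal sequences of the features". Sequence length is still to be adjusted to improve the predictions, and the feature-selection method may be chosen separately for each score.

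Discussion: "Multivariate linear models for brain functioning scores will be obtained by using supervised machine/deep-learning and cross-validation". On the reference: "Each brain functioning scores estimated by each biometric model will be agreed with each score of one or some questionnaires".

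Other sections bear on how many labels exist. Table 2 and the section on questionnaires and neuro-assessments give the WISC-V subtests and questionnaires once per visit. Study design re-assesses 10% of participants. Sampling sets the final sample at 400 children.

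The article does not state the unit by which folds are formed. Nesting within participants is recognised in the hypothesis testing framework, but only for the mixed models. Over- and underfitting are named in the Discussion as biases to review, without a rule.

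**The concern.** Two things are run together: the number of input rows and the number of independent labels. Many sequences from one child give a recurrent network or transformer more to train on. They do not give it more children whose WISC-V or questionnaire score is known. For learning the link between signal and score, the second number is the one that limits what can be learned and how precisely it is known.

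This matters for validation. Face, posture and touch style are likely to be stable within a session. If sequences from one child fall on both sides of a split, a flexible model can recognise the child and return that child's score without having learned anything about the trait. This happens even when features and model are fixed in advance, so it is separate from optimism due to feature selection. Tuning sequence length and selecting features on such folds would then favour whatever identifies the child best.

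Table 1 places strong correlation between paper-based performance and biometrics among the hypotheses for the primary objective. If the biometric scores entering that comparison are model predictions, leaking folds would inflate the correlation, and an interval computed over samples would be too narrow.

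**Working it through.** **The plan's own figures.** The AI modeling section gives no sample count, accuracy or validation figure to reproduce. The number of children can be checked against Sampling: 400 / 0.8³ = 781.25, rounded up to 782, against 786 stated; forwards, 786 × 0.8³ = 402. So 400 children is consistent with the plan's own attrition rule. It is the figure used below.

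**Number of labels.** One set of reference scores per child per visit, with 10% seen twice: 400 + 0.10 × 400 = 440 sets, from 400 independent children. (The caption of Figure 1 gives a different number returning at 2 months. The count of children does not depend on it.)

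**Assumptions, not in the documents.** 60 windows per child, hence 400 × 60 = 24,000 rows; 10 features; within-child correlation (ICC) of the features of 0.2, 0.5 or 0.7.

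**Simulation.** Each feature is √ICC × (child component) + √(1 − ICC) × (window noise). Each child receives one random label unrelated to the features, so the true correlation is 0. The learner is 5-nearest-neighbour with 5-fold cross-validation and 2 replicates per ICC. The per-child figure correlates the mean prediction of a child's windows with that child's label.

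| ICC | Split by window: r per window | Split by window: r per child | Split by child |
|---|---|---|---|
| 0.2 | 0.02 | 0.15 | about 0 |
| 0.5 | 0.24 | 0.66 | about 0 |
| 0.7 | 0.62 | 0.87 | about 0 |

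Repeat runs agree to within about 0.03.

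**Sensitivity to learner and ICC.** A second simulation used 10 samples per child and 20 features, split by sample, with r per sample:

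| ICC | 3-nearest-neighbour | Kernel ridge | Linear ridge |
|---|---|---|---|
| 0 | 0.00 | −0.01 | 0.00 |
| 0.1 | 0.01 | −0.03 | 0.01 |
| 0.3 | 0.08 | 0.19 | 0.08 |
| 0.5 | 0.44 | 0.51 | 0.12 |
| 0.8 | 0.99 | 0.85 | 0.17 |

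With 100 features the linear figures rise to 0.20, 0.29 and 0.38 at ICC 0.3, 0.5 and 0.8, and 3-nearest-neighbour gives 0.69, 0.997 and 1.00. Split by child, every scenario lies between −0.05 and 0.04.

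**Standard error.** Treating 24,000 windows as independent gives 1/√24,000 = 0.0065 for a correlation near 0. The label is constant within a child, so the understatement is √(1 + 59 × ICC):
- ICC 0.2: √12.8 = 3.6
- ICC 0.5: √30.5 = 5.5
- ICC 0.7: √42.3 = 6.5
- upper limit, ICC 1: √60 = 7.7, which is the ratio of 1/√400 = 0.05 to 0.0065

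**The case against.** The strongest reply is that the article never says folds are cut by sample. It describes training input in one section and mentions cross-validation in another, and a condensed article may leave the fold unit to a fuller plan. That stands as far as it goes: a reader might infer that sample-level splitting is planned, and the text does not support this. The statement that samples add to the learning data is nevertheless written out, it is the only unit of learning data the AI section promotes, and no other unit is attached to the cross-validation. Followed literally, it leads to the leaking split.

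Second, the cross-validation sentence has multivariate linear models as its subject, and for linear models the false correlation is weak to moderate. This also stands, and it limits the size. But the same sentence says the models "will be obtained by using supervised machine/deep-learning and cross-validation", and the AI modeling section chooses recurrent networks and transformers. The article does not separate the two.

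Third, a single label per run is said of the classical approach, while the dynamic one predicts a score at an instant. A reader might infer that every child has exactly one label. The precise position is one set of reference scores per visit, several target scores, and a second visit for some. No reference measured within the run is described, so the number of children behind each score is unchanged.

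Fourth, more sequences do help a sequence model to train, and no standard error over samples is actually planned. Both are fair. The first is why the sentence needs rewording and need not be deleted. The second makes the standard-error figures a conditional warning.

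**Conclusion.** The point holds as a wrong statement about the information in the data, together with a validation unit that must be fixed. Within-child samples are presented as a gain in learning data, while each reference score rests on about 400 independent children. If folds follow that count, a flexible model can show apparent prediction from noise: per-child r of about 0.15, 0.66 and 0.87 at ICC 0.2, 0.5 and 0.7 under the stated assumptions, and about 0 when children are split. Standard errors over samples would be 3.6 to 6.5 times too small at those ICCs.

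It would go too far to say that the trial will report strong prediction from noise. The result depends on within-child correlation and on model flexibility, and the documents give no figure for the first. The effect is negligible at ICC near 0 and smaller for linear models. Window count, feature count and ICC are assumptions, and simple learners stand in for the networks. A 7.7-fold understatement of the standard error is the limit at ICC 1, not the expected value.

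**What to change.** 1. Reword the sentence in AI modeling: extra samples per run add training input but not independent labels, of which there are about 400 children per score.
2. State that the child is the unit of every split, with all samples and both visits of a child kept in one fold.
3. Carry out feature selection and the tuning of sequence length inside the training folds only.
4. Report performance and its confidence interval on one value per child.

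A run that leaves out one site at a time would show whether site or device is being learned. It is optional.

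The cost is a few lines of text and a grouped split in the analysis code, with no new data. Reported performance may be lower. If the full plan already splits by child, tunes inside the training folds and reports one value per child, only the article's wording needs to change.

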### Study design

EPIDIA4Kids is an observational uncontrolled multi-center study (several cities in France) during which no treatment or placebo will be administered. Complementing children’s assessment at baseline (T0), a subsample of 10% of the participants will be re-assessed after 2 months (end-T2). At least one of the parent or legal representatives and children will also answer questionnaires and will be interviewed using a semi-structured instrument (Figure 1).

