#### Reference interval

There are several methods for constructing a reference interval for psychometric measures based on age and gender, all of which require a larger number of subjects the higher the precision desired. The minimum number of observations required per group has been set at 120 and reaffirmed in the National Committee for Clinical Laboratory Standards guidelines (65). For a 95% confidence interval around each percentile at the ends of the reference interval, this number increases to 153, and to 199 for a 99% confidence interval.

We will thus examine performance on neuropsychological tests, questionnaires, and academic assessments by:

▪ A univariate ANOVA to test for main effects and moderating effect of a qualitative variable.▪ Linear multiple regressions and conditional analysis to test the moderating effect of a quantitative variable.▪ And multiple linear regressions to test a mediating effect.

Machine- and deep-learning approaches will be used also to map the multi-dimensional of the cognitive, emotional, and behavioral measures. Unsupervised machine learning approaches will be to identify groups of children across dimensions and define transdiagnostic profile according to common cognitive, emotional, or behavioral profiles. Such methods will include class-based analyses (e.g., latent class or cluster analyses) and clustering algorithms.

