#### Hypothesis testing framework

Hypotheses will be tested at the α = 0.05 level after adjustment for multiple tests. Significant statistics only will be converted to indices of effect size and their associated confidence interval. The primary analytical framework will be nested linear mixed models with random effects (LMEs), and Cox proportional hazards models to handle quantitative predictor variables and categorical variables.

For LMEs, the primary effects of interest will generally be the interaction between independent variables and time (e.g., the visit number). Analyses will be performed with multiple levels of nesting (e.g., site, devices) that are not of intrinsic interest, as well as nesting within participants over time, allowing all data to be used for wide analyses. Age and gender will be specified as co-variables and others such as demographic and other background variables will be specified upon scientific and empirical considerations.

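### The AI modelling steps are said to find causal relationships, but feature extraction and feature selection in this observational study can show only predictive association

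*Protocol article*

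**What the plan says.** The AI modeling section of the Protocol article describes three steps, and the first two carry a causal claim.

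- Step 1 is the extraction of high-level features, validated by psychologists and physicians. The choice is justified by the need to explain the system's outputs, because it allows one "to find the causal relationships between them the target variables and the input features".
- Step 2 is variable selection. It is said to help "detect causal relationships between high-level behavioral characteristics and the variables to be predicted", with children's attention scores as the example. The methods "can be supervised or unsupervised machine learning methods", and during learning "several methods can be tested to find the best one for each attention score".

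Study design states that "EPIDIA4Kids is an observational uncontrolled multi-center study", with no treatment or placebo given.

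Reference interval adds "multiple linear regressions to test a mediating effect" and names no exposure, mediator, outcome or visit. Hypothesis testing framework says, for the linear mixed models, "Age and gender will be specified as co-variables", with site as a nesting level and further covariates left open. The AI modeling section states no such adjustment for the AI pipeline.

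**The concern.** A causal claim needs something that feature extraction and selection do not provide: manipulation of the feature, or a stated causal model with a defensible set of confounders. A supervised selector ranks features by how well they predict. It keeps a feature that merely shares a cause with the target and may drop a true cause that is redundant given others. An unsupervised selector does not use the target at all. Expert validation makes features interpretable; it does not identify causes.

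What is at stake is how the output is read. The feature list is there to explain the tool's results. The tool description says that the AI module will support clinical recommendations, and the Discussion foresees support for diagnostic and therapeutic decisions. A list labelled causal would invite conclusions about why a child scores as he or she does, which these data cannot support.

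**Working it through.** The document gives no figure for this claim, so there is nothing to reproduce. The check is first one of logic, then an illustration of size.

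**Claim against design and method**

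- Design: observational and uncontrolled. No game feature is manipulated.
- Method in step 2: the best-performing of several selectors, chosen score by score. The criterion is prediction.
- Order of measurement: the Abstract and the section on questionnaires and neuro-assessments place the neuropsychological tests before the games at the same visit. Where such a score is the target, it is recorded before the features said to cause it. A stable trait that drives both is a ready explanation.
- Assumptions: the article gives no causal model and no confounding assumption to support the claim.

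**Illustration**

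Inputs from the document: n = 400 (Sampling) and α = 0.05 (Hypothesis testing framework), taken as two-sided and without multiplicity adjustment. Assumed, not in the document: one unadjusted common cause U, and equal loadings L of feature X and score Y on U. The true effect of X on Y is set to zero.

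X = L·U + √(1 − L²)·e₁ and Y = L·U + √(1 − L²)·e₂, so corr(X, Y) = L².

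Probability of significance (Fisher z) ≈ Φ(atanh(r)·√(n − 3) − 1.96), with √397 = 19.92.

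- L = 0.3: r = 0.09, atanh(r) = 0.0902, product 1.798. Φ(1.798 − 1.96) = Φ(−0.162) = 0.436.
- L = 0.5: r = 0.25, atanh(r) = 0.2554, product 5.089. Φ(5.089 − 1.96) = Φ(3.129) = 0.999.

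A simulation with 2,000 replicates per row agrees. Its last column covers a mediation regression (product of coefficients, Sobel test). There the mediator and the outcome share U, the mediator has no effect on the outcome, and the exposure-to-mediator path is an assumed 0.3.

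| L | corr(X, Y) | Feature falsely significant | Mediation falsely significant |
|---|---|---|---|
| 0 | 0 | 0.052 | 0.044 |
| 0.3 | 0.09 | 0.439 | 0.421 |
| 0.5 | 0.25 | 0.999 | 0.9995 |
| 0.7 | 0.49 | 1.000 | 1.000 |

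Without a common cause the error stays near 5%. With one, it rises with L, and a larger sample would raise it further, because the correlation is real and only its causal reading is false.

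**The case against.** Several points on the other side are fair.

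- **The module is for prediction.** A feature that shares a cause with the target is legitimate there, and no objective, outcome or hypothesis in Table 1 or the lists of aims is a causal estimand. This stands. It limits the point to what may be claimed from the feature list.
- **Only one of the two sentences concerns selection.** A reader might infer that the article twice claims causal discovery by feature selection. It does not: the sentence in step 1 concerns extraction. The claim is still made twice, and neither step can support it.
- **The mediation regressions.** A reader might infer that they use variables from a single visit. The article names no visit and no variables. Some candidate exposures, such as age or a previous diagnosis, precede the scores. The wording there is also less explicit than in the AI modeling section. So the criticism is conditional: without time order and confounding assumptions, a mediation conclusion is not supported. Those details may stand in the full protocol or analysis plan.
- **Age and site.** The mixed models adjust for age and gender and handle site by nesting, so age is a weak example of an unadjusted confounder there. General ability and medication are not fixed covariates even in those models.
- **The numbers.** The loadings are assumptions, the result depends strongly on them, and the article names no marginal test as its selection rule. This stands; the figures show how large the problem can be and do not measure an error in the plan.
- **Time series.** The signals have order within a session. That supports prediction from past signals but does not remove confounding by stable traits of the child.

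**Conclusion.** The point holds as a correction of a stated claim. The AI modeling section attributes causal findings to feature extraction and to variable selection, and neither the observational design nor the methods named can deliver them. They can show predictive association.

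Under one unadjusted common cause with assumed loadings of 0.3 to 0.5, a feature with no effect would be significant in a marginal test at n = 400 with probability about 0.44 to above 0.99. The conclusion does not depend on these values; they only show that the risk need not be small.

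A reader might go further and conclude that the prediction models are invalid or that the study's main objectives rest on causal inference. The document supports neither. Nor does the point depend on how many children are seen twice. Study design gives a 10% re-test at 2 months, the legend of Figure 1 about 500 returning, and Table 1 a 4-month follow-up. These places must be reconciled separately.

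**What to change.** 1. In both sentences of the AI modeling section (steps 1 and 2), replace 'causal relationships' by 'predictive associations'.
2. Present the selected features as predictors of the scores, not as mechanisms, wherever they are used to explain the tool's output.
3. Report the mediation regressions in the Reference interval section as exploratory associations, unless exposure, mediator and outcome are named and their time order and confounding assumptions are stated.

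Reporting how stable the selection is over resamples would not answer this point, since a confounded feature can be selected very consistently.

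The cost is a change of wording and a weaker claim. Endpoints, sample size, data collection and prediction models stay as they are.

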### Participant

The inclusion criteria will be: (i) boys or girls of any ethnicity, aged 7–12 years (typically developing and diagnosed with NDDs); (ii) French native speakers; (iii) normal hearings, normal or corrected-normal vision; (iv) no brain trauma; (v) an estimated intelligence quotient of 85 and above (exclusion if score < 25th percentile) based on Weschler’s subtests Matrix Reasoning and Similarities (50); (vi) no history of co-morbid psychiatric illness that might confound the analysis of the study (e.g., schizophrenia, obsessive-compulsive disorder, major depression, or bipolar disorder); (vii) ADHD medications and Selective serotonin reuptake inhibitors (SSRIs) are not exclusionary since use of these medications is associated with neurodevelopmental disorder condition, but the treatment will be suspended 2 days before any cognitive evaluation.

The exclusion criteria will be: (i) failure to meet the inclusion criteria; (ii) lack of written informed consent: the child and at least one of the parents (or the legal representative) must sign the informed consent form.

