### Questionnaires and neuro-assessments

All questionnaires and neuro-assessments are summarized in Table 4. At baseline and T2-end, the visit will be conducted in a sequential manner with breaks. First, children will perform neuropsychological assessments through digitalized or paper/pencil WISC-V battery [1.5 h, (50)] with the Similarities, Vocabulary, Coding, Symbol search, Block design, Digit, Matrix reasoning subtests. Secondly, questionnaires will be answered digitally for:

▪ Demographic information (age, gender, language spoken, family structure, school, previous diagnosis for neurodevelopmental disorder) and scoring of manual laterality [Edinburgh handedness, short version, 4 items (54), estimated intellectual quotient (50), and sleep quality (Pittsburgh Sleep Quality Index, 11 items) (55)].▪ The French version of the ADHD-Rating Scale (56) incorporating the 18 criteria rating Inattention (sum of odd items scores) and Hyperactivity-Impulsivity (sum of even items scores) symptoms.▪ The French version of the Children Behavior Check List [short version, 32 items, (57) and Conners-3 (58)—psychopathological behavioral or emotional traits].▪ The Autism Quotient List French version scoring [10 items, (59)]—psychopathological behavioral or emotional traits.▪ The Developmental Coordination Disorder Questionnaire [DCDQ, 15 items, (60)].▪ The Behavioral assessment of executive function scoring [BRIEF, 72 items, (61)].▪ The French versions of the School Motivation Questionnaire [SMQ, 44 items, (62)] and the Grit-Scale for Children and Adult [GSCA, 12 items, (63)].

**Table 4 tab4:** Explanatory variables for the XAI4Kids^®^ e-measurement tool.

Neuropsychologic tests	Variables
	Reaction time: average reaction time (RT) for every executed task
	Hits: number of correct answers
	Total errors: total number of errors
	Wrong answers: number of answers that are not omission, perseverance and outliers
	Omission: reaction time = 0 ms
	Distractors: number of answers looking similar to the target answer
	Persévérance: 0 ms < reaction time < 100 ms
	Outliers: standard deviation of reaction time (exécution) < 3 x standard deviation (si RT≠0)
	Hits RT: median of reaction time for correct answers
	Hits RT SE: standard error de Hits RT
	SE variability: standard deviation of the 3 standard errors calculated for each task block (mesure of the participant variability)
	Hits rt block change: slope change for RT between blocks (vigilance)

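### The optional NDD/neurotypical classification rests on clustering of behavioural features, with nothing stated that ties either cluster to the recorded diagnosis, so its diagnostic labels may reflect noise, age or other shared variation.

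*Protocol article*

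**What the plan says.** The third step under AI modeling predicts scores with recurrent networks and transformers. It then offers a second feature as an optional addition: "classifying the children (NDD/neurotypical) starting only from the high-level features extracted from the raw behavior signals, without the need for labels". A parenthesis directly after these words identifies the labels as attention scores. The method follows: "In this case, unsupervised learning models of the “clustering” type are applied". Neither the algorithm nor the number of clusters is named.

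Other parts of the article bear on this:

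- **Participant:** the sample mixes both kinds of children, "aged 7–12 years (typically developing and diagnosed with NDDs").
- **Questionnaires and neuro-assessments:** the demographic items include "previous diagnosis for neurodevelopmental disorder", so a diagnostic reference is on file.
- **Table 4:** the candidate features are reaction times, hits, errors and tracking measures.
- **Hypothesis testing framework:** age and gender are covariates in the mixed models. No such adjustment is stated for the clustering.
- **Reference interval:** a separate, planned use of clustering is described: "Unsupervised machine learning approaches will be to identify groups of children across dimensions and define transdiagnostic profile".

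**The concern.** The article states a rule here; this is not a detail left open. The inputs are behavioural features and the output is one of two diagnostic names. A clustering algorithm groups children who resemble each other on whatever varies most across the features. It has no knowledge of NDD, and no later step is described that would test whether either group corresponds to it.

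The primary objective names sensitivity, specificity and predictive values, and the tool is hypothesised to act as a first-line evaluation for NDDs. If the option were used as written, a child could be called NDD because of cluster membership that has nothing to do with NDD, and the analysis would not reveal it.

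**Working it through.** **No figure to reproduce.** The article gives no number of clusters, accuracy, feature-age correlation or NDD share for this step. What follows is an illustration under stated assumptions.

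**Inputs from the article:** N = 400 (Sampling) and ages 7 to 12 (Participant).

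**Assumed:** two clusters by k-means; 20 standardised features; age uniform from 7 to under 13; NDD share π = 0.25, independent of age; 40 replicates per scenario. Each feature is x = r·age(z) + g·G + √(1 − r² − g²)·e + δ·NDD, where r is the feature-age correlation before the NDD shift, G a shared factor unrelated to age, and δ the NDD shift in SD on every feature.

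**Step 1: no age effect and no NDD effect (r = g = δ = 0).** The split is about 47/53. Kappa with diagnosis is 0.03, even though the cluster names are chosen to favour agreement, and |r| with diagnosis is 0.04. Chance alone gives an expected |r| of √(2/π)/√400 with π = 3.14…, which is 0.798/20 = 0.04. With 300 of 400 children neurotypical, naming one cluster NDD would label 0.47 × 300 = 141 or 0.53 × 300 = 159 of them NDD, depending on which cluster takes the name.

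**Step 2: adding age and NDD effects, g = 0.** Cells show |r| of the split with age / with diagnosis.

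| NDD shift δ | r = 0 | r = 0.2 | r = 0.3 | r = 0.5 |
|---|---|---|---|---|
| 0 | 0.04 / 0.04 | 0.56 / 0.04 | 0.72 / 0.04 | 0.82 / 0.03 |
| 0.3 SD | 0.03 / 0.24 | 0.51 / 0.31 | 0.68 / 0.25 | 0.81 / 0.15 |
| 0.5 SD | 0.04 / 0.60 | 0.45 / 0.47 | 0.61 / 0.39 | 0.77 / 0.27 |
| 0.8 SD | 0.04 / 0.88 | 0.26 / 0.72 | 0.46 / 0.58 | 0.68 / 0.41 |
| 1.0 SD | not run | 0.15 / 0.86 | 0.34 / 0.70 | 0.62 / 0.48 |
| 1.5 SD | not run | 0.05 / 0.99 | 0.07 / 0.95 | 0.43 / 0.68 |

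**Hand check.** Per feature, age contributes shared variance r² and diagnosis contributes δ²·π(1 − π) = 0.1875·δ². They balance at r = δ·√0.1875 = 0.433·δ, that is r = 0.13, 0.22, 0.35, 0.43 and 0.65 for δ = 0.3, 0.5, 0.8, 1.0 and 1.5. Wherever δ > 0 in the table, age leads above that value and diagnosis below it.

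**Step 3: a shared factor unrelated to age (g = 0.4, r = 0.2).** The correlation with age falls to 0.27–0.33 for δ from 0 to 0.8. At δ = 0.5 the pair is 0.30 / 0.32, so neither age nor diagnosis governs the split.

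**Step 4: features residualised on age before clustering (g = 0, r = 0.2 to 0.5).** The correlation with age falls to 0.02–0.03. With diagnosis it is 0.26–0.34 at δ = 0.3, 0.62–0.69 at δ = 0.5 and 0.89–0.95 at δ = 0.8. With δ = 0 the two-way split of about 47/53 remains and is still unrelated to diagnosis. Age adjustment removes the age confounding but not the forced split.

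**The case against.** The strongest reply is that this is an optional feature beside a supervised route. The tool's stated main output is score prediction, and the Discussion describes supervised learning with cross-validation. The Figure 2 caption speaks of validating the selected metrics against NDD-related states, and the Discussion concedes that the biometrics need mix adjustment relative to clinical categories. The optional status stands and limits the weight of the point. The general remarks do not answer it: they are not attached to the cluster labels and give no method.

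Five stronger readings are tempting, and the documents do not support them.

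- *The split mainly tracks age.* No age correlation or NDD effect is given. The table shows that either can lead.
- *Two groups appear whatever the data show.* That holds only if two clusters are fixed in advance, which the class names imply but the text does not state.
- *The article dispenses with diagnostic labels.* The labels it calls unnecessary are attention scores. That diagnosis plays no part in forming the clusters follows from using behavioural features alone in an unsupervised method.
- *Younger typical children would be called NDD.* Without a naming rule, this cannot be derived.
- *The claim to capture NDD heterogeneity would follow from any data set.* That claim does not rest on this option.

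The absence of a rule for the number of profiles under Reference interval is a detail that an article may leave to the full plan, so it is not counted here. It can also fairly be said that training on recorded diagnosis sits uneasily with a study that regards NDDs as under-detected and is critical of categorical diagnosis. That is a real cost. It does not justify giving diagnostic names to unanchored clusters.

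**Conclusion.** The point holds in limited form. As written, the optional classification gives diagnostic names to clusters formed without diagnosis or age, and the article describes no anchor to the diagnosis it collects. With two clusters and no NDD effect, groups of roughly equal size still appear, with kappa against diagnosis of about 0.03.

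How far age would drive the labels is not settled. At an NDD shift of 0.5 SD, |r| with age against diagnosis runs from 0.45 against 0.47 (feature-age correlation 0.2) to 0.77 against 0.27 (correlation 0.5). At 1.5 SD diagnosis dominates throughout. These magnitudes are illustrative. They rest on assumed k-means with two clusters, 20 features, a 25% NDD share and diagnosis independent of age. The lack of anchoring rests on the text alone. The change is worth making but is not critical, because the feature is optional.

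**What to change.** 1. Give clusters no diagnostic names.
2. Base any NDD/neurotypical classification on the recorded diagnosis, with age and sex as inputs. Report cross-validated sensitivity, specificity and AUC with confidence intervals. Keep all of a child's data in one fold, because the dynamic approach yields many samples per child.
3. Keep clustering as a descriptive analysis. Run it on age- and sex-adjusted features, allow a one-cluster result (for example by a gap statistic or parametric bootstrap against one cluster), and compare the resulting clusters with recorded diagnosis.

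The cost is revised wording and modest extra analysis. Diagnosis, age and gender are already collected. There are two downsides. Recorded diagnosis is an imperfect label because NDDs are under-detected, so apparent false positives may include undiagnosed children. The feature also gives up its claim to need no labels.
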